## 5.3 Definition of a suspected unexpected adverse reaction (SUSAR)

A SUSAR is an event whose nature, intensity, and course are at odds with the actions performed in this research.

## 5.4 Course of action in the case of a serious adverse event

The declaration of a serious adverse event occurring within 6 days following a sample will be made within 24 hours of the event to the Department of Clinical Research and Development via the faxing or email of the serious adverse event notification form.

### ***Département de la Recherche Clinique et de l'Innovation***

[contact]

[contact]

email: [[contact]](mailto:[contact])

The investigator will note for each event:

- its description, as clearly as possible and according to the medical terminology.
- the start and end dates of the event.
- the measures taken and the need or not for corrective treatment.
- its course that, in the event of a non-fatal event, should be followed until recovery, a return to the previous status, or stabilization of any sequelae.
- the causal relationship between this event and the samples taken as part of the study.
- the causal relationship between the disease being treated and another pathology.

A follow-up report will then be sent to the sponsor to document the evolution of the event by completing the various follow-ups of the initial SAE declaration form.

## **VI – STATISTICS**

### **6.1 Description of planned statistical methods**

Qualitative data will be presented in the form of counts and percentages. The quantitative data will be summarized, with the associated 95% confidence intervals, by the mean, standard deviation, median, and extreme values.

The investigation of the relationship between the histological and clinical variables and the molecular alterations will be performed using chi-square or Fisher, Wilcoxon, or Kruskal-Wallis tests depending on the nature of the data collected.

Overall survival and recurrence-free survival will be evaluated via the Kaplan-Meier method from the date of initial diagnosis and from the date of treatment start post-biopsy. Survival comparisons of different groups of molecular alterations will be performed using log-rank analysis. Prognostic studies on overall survival and progression-free survival will be performed at the end of the study.

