received the corresponding treatment. For 18 of these, progression-free survival with their treatments lasted more than 1.3 times the length of progression-free survival with previous treatment. The same concept was tested in metastatic breast cancer in the French SAFIR01 trial with promising results. Their analysis of metastatic samples included the search for amplifications in the pan-genome CGH-array and mutations in mTOR pathway (*PI3K*, *PTEN*, *AKT*) genes to see if molecular targets were present that allowed for the referral of the patient to an early trial of targeted therapies. A workable genomic profile was obtained in 64% of patients, 69% of whom had a molecular abnormality of interest for which a targeted drug existed. A targeted personalized treatment was delivered to 43/423 patients with regression or stabilization of the disease of at least 4 months in 13 cases (4). Additional prospective studies are currently underway in France that are testing this concept in patients with all types of metastatic solid tumors: the MOSCATO trial (MOlecular Screening for CANcer Treatment Optimization), sponsored by the Gustave-Roussy Institute; the MOST (My Own Specific Treatment) trial, sponsored by the Léon Bérard Center; and the SHIVA trial, sponsored by the Curie Institute (5). The SHIVA trial plans to evaluate this strategy in a randomized setting for the first time, comparing it to a conventional approach in patients with a molecular abnormality that is potentially targetable by known therapies (imatinib, everolimus, vemurafenib, sorafenib, erlotinib, lapatinib + trastuzumab, dasatinib, tamoxifen, or letrozole). Personalized medicine programs are also underway in several countries: the MD Anderson Cancer Center (6), [name] team in the USA (7), and Toronto in Canada (8). In these studies, typing is performed on a metastatic sample rather than the original tumor due to the appearance of new molecular alterations and resistant clones during tumor progression that may alter therapeutic indications.

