### **III – ELIGIBILITY CRITERIA**

The project is based on the collection and analysis of biological tumor and blood samples for any patient treated at our Institute for advanced malignant solid tumors (metastatic or locally advanced) progressive during at least one line of prior systemic therapy. All cancer types will be included whether they are common or rare cancers for which treatment options are even more limited at an advanced stage.

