#### **3.1 Inclusion criteria**

- Age  $\geq$  18 ans.
- Histological cancer diagnosis.
- Locally advanced or metastatic stage, with tumor lesion accessible for biopsy.
- ECOG PS  $\leq$  2 (Appendix 1).
- Affiliated with or benefiting from social security.
- Signed informed consent form for participation in the study.

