### **4.2 – Biological sampling at inclusion (cf Appendix 2)**

#### **4.2.1 - Tumor samples (locally advanced tumor or metastasis): biopsies or surgical specimens**

The sampling sites will be determined by the investigative team based on its accessibility and volume. Bone and brain metastases will not be sampled. At least 3 tumor fragments will be taken for each patient and sample site selected.

These fragments will be obtained:

- either via biopsy performed with radiological or endoscopic monitoring in the Radiology Department or the Medical-Surgical Exploration Unit (*Unité d'Explorations Médico-Chirurgicales*), respectively. The sample may be taken, depending on the location of the site selected:

- by percutaneous image-guided biopsy (ultrasound or scanner), mainly using 14, 16, or 18-gauge needles via a manual, semi-automatic, or automatic mechanism. The radiologist will select the most suitable technique and type of needle for each sample.
- by biopsy at the end of an endoscopic ultrasound examination, mainly using 19 or 22 gauge needles that are 8 cm long. Biopsies are obtained by aspiration with a 20 ml syringe with a back-and-forth movement in the tumor; 1 to 3 passes are necessary to obtain a microbiopsy.

The number of biopsy fragments taken will be limited to 5 fragments per target (biopsy site) and the total number of biopsy fragments taken, all targets combined, will be limited to 10 fragments.

- or via surgery performed in the Surgery Department.

The collected fragments will be transferred to the Pathology Department. These will include:

- a fragment to be frozen for storage at the Biological Resources Center (BRC) for the immediate extraction of nucleic acids after verification of tumor cellularity, which will be noted in the report. Only samples with a cellularity greater than 30% will be taken into account. The CRB will be responsible for the storage and extraction of nucleic acids until recovered by the Molecular Oncology and Molecular Oncogenetics laboratories for genomic analysis.
- a fragment fixed and embedded in paraffin will be stored in the Pathology Department for additional immunohistochemical or biological studies.
- at least one fragment to be frozen, after verification of tumor cellularity, for storage in the CRB at -80 °C or in liquid nitrogen (depending on the mode of preservation of the tissue; in a cryotube in nitrogen or a bag at -80 °C) for subsequent proteomic and/or genomic molecular studies.

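### Survival counted from initial diagnosis includes the time before inclusion, when no enrolled patient could die; the alteration log-rank is not kept off that origin and can mistake entry time for prognosis

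*Protocol*

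**What the plan says.** Section 6.1 gives two time origins for the survival curves. The sentence begins "Overall survival and recurrence-free survival will be evaluated via the Kaplan-Meier method from the date of initial diagnosis" and goes on to add a second origin, the start of treatment begun after the biopsy. The next sentence reads "Survival comparisons of different groups of molecular alterations will be performed using log-rank analysis" and names no origin. Prognostic studies of overall and progression-free survival are to follow at the end of the study, again with no origin given.

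Entry comes later than diagnosis. Section III describes the population as patients with "advanced malignant solid tumors (metastatic or locally advanced) progressive during at least one line of prior systemic therapy". The list in section 3.1 requires "Locally advanced or metastatic stage, with tumor lesion accessible for biopsy" and an ECOG score of at most 2, but does not repeat the condition on prior treatment. Section 4.2 takes the tumor sample at inclusion, and section 4.4 types the alterations on it. Section 4.5 follows patients for 3 years.

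Section 1.3 explains that comparable studies type metastases rather than the original tumor "due to the appearance of new molecular alterations and resistant clones during tumor progression". Section 2.2 makes the relation of alterations to progression-free and overall survival a secondary objective in the most frequent diseases.

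The protocol does not mention delayed entry, left truncation, a landmark, or adjustment for time from diagnosis to inclusion.

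**The concern.** A patient who dies between diagnosis and inclusion never enters the data set. Kaplan-Meier from diagnosis nevertheless places every enrolled patient in the risk set from day zero, so the early risk sets hold people who could not have died there and still be observed.

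This has two consequences. First, the curve describes only patients who lived to inclusion and lies above the survival of all patients from diagnosis whenever some die earlier. Second, a log-rank from diagnosis compares the sum of time to inclusion and survival after inclusion. Groups that reach inclusion at different speeds will separate even if their mortality afterwards is identical. An alteration more common in late entrants would look favorable, and one more common in early entrants would look harmful.

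At stake is the secondary objective on survival by alteration. Section 6.2 adds 100 patients to enlarge the subpopulations for the secondary objectives. More patients would make a biased comparison more precise without correcting it.

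**Working it through.** **The plan's own figures.** The protocol gives no survival estimate, event count or power. Its one sample-size calculation can be reproduced: 300/(1 − 0.35) = 461.5, against the stated 460. It has no bearing on this point.

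**Inputs.** From the protocol: 36 months of follow-up (section 4.5), entry conditional on being alive with advanced disease (sections III and 3.1), and typing at inclusion (sections 4.2 and 4.4). Assumed, because the protocol does not give them: 50 patients per group, exponential time from diagnosis to inclusion, and exponential survival after inclusion with a 12-month median.

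**1. Log-rank from diagnosis when survival after inclusion is identical** (simulation, nominal level 5%).

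| Mean months to inclusion, group A vs B | Rejection, time from diagnosis | Apparent hazard ratio |
|---|---|---|
| 24 vs 24 | about 5% | 1.0 |
| 36 vs 24 | about 34% | 0.71 to 0.72 |
| 48 vs 24 | about 80% | 0.53 to 0.57 |
| 60 vs 24 | about 95% | 0.42 to 0.50 |

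Repeat runs gave rejection of 32 to 36%, 77 to 80% and 94 to 96% in the last three rows. The hazard-ratio ranges reflect different estimators; a one-step estimate exaggerates large effects. With time counted from inclusion, rejection is about 5% in all rows.

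**2. A second model.** This one has 560 entrants, 30% of them carriers, the same exponential survival from diagnosis in both groups, and enrollment only if alive at entry. Doubling the carriers' mean entry time gives a hazard ratio of 0.76 to 0.82 and 31 to 45% rejection. Tripling it gives 0.67 to 0.73 and 71 to 82%. Equal entry times give 0.99 to 1.01. Counting from entry restores 0.99 to 1.01 throughout.

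**3. How far the level is overstated.** Let entry occur at rate a = 1/24 = 0.0417 per month, death before entry at rate c, and death after entry at rate b = ln 2/12 = 0.0578. With r = a + c:

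- Share dying before entry = c/r.
- Survival of all patients from diagnosis: S(t) = exp(−rt) + [a/(b − r)]·[exp(−rt) − exp(−bt)].
- Survival of enrolled patients, which the planned curve targets: S(t) = [b·exp(−rt) − r·exp(−bt)]/(b − r).

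Example with c = 0.005: r = 0.0467 and c/r = 11%. At t = 30.5, exp(−rt) = 0.241 and exp(−bt) = 0.172, so the first S is 0.241 + (0.0417/0.0111)(0.241 − 0.172) ≈ 0.50.

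| Death rate before entry (per month) | Die before entry | Median, all patients | Median, enrolled patients |
|---|---|---|---|
| 0 | 0% | 34.5 | 34.5 |
| 0.005 | 11% | 30.5 | 32.4 |
| 0.01 | 19% | 27.3 | 30.7 |
| 0.0578 (equal to later rate) | 58% | 12.0 | 22.6 |

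The overstatement is nil in the first row and about 2, 3 and 11 months in the others. It depends on how many patients are lost before entry.

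**4. Does delayed entry repair the level?** In simulations of these four settings, Kaplan-Meier with entry to the risk set at inclusion gave medians of 13.5, 12.7, 13.5 and 11.0 months. Only the last is close to the true median. Delayed entry assumes that the hazard at a given time since diagnosis is the same before and after entry. Section III makes progression a condition of entry, so that assumption is doubtful here. Delayed entry performs well in the model of step 2 only because that model builds the assumption in.

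**The case against.** The strongest reply is that the protocol already plans an unaffected analysis. The post-biopsy origin lies after sampling, and the log-rank sentence does not name diagnosis, so a later analysis plan could settle the matter. The first part stands: the second origin is free of this problem. The second part does not remove the point, because section 6.1 itself names diagnosis as an origin and leaves the group comparison open to it.

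A reader might infer that late acquisition makes carriers late entrants by construction. The protocol does not establish this. Section 1.3 gives a general reason for typing metastases; it does not say which alterations arise late or that carriers in this cohort enter later. With equal entry times the log-rank keeps its nominal level.

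A reader might also take the gap between a median of about 34 months from ordinary Kaplan-Meier and about 12 with delayed entry as the size of the error. That holds only if mortality before progression equals mortality after it. If few patients die before entry, the ordinary curve is nearly right and delayed entry is far off.

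Finally, if groups truly differ in time to advanced disease, their survival from diagnosis truly differs. The 34% to 95% are therefore false positives about survival after inclusion, not necessarily about survival from diagnosis. This stands too, and it is why the result could not be read as an effect on prognosis after typing.

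**Conclusion.** The flaw is real but confined to the diagnosis origin. Its direction for the survival level follows from the entry rule: overstated, by nothing if no one dies before inclusion and by about 2 to 11 months in the median under the assumed pre-entry mortality of 11% to 58%. For the comparison of alteration groups, the bias needs a difference in time to inclusion, which section 1.3 makes plausible but does not prove, and it can run either way. Where mean entry times differ by a factor of 1.5 to 2.5, with the assumed 50 patients per group, the log-rank from diagnosis rejects in roughly 34% to 95% of cases despite identical mortality after inclusion.

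The documents do not support the stronger conclusion that the secondary objective will be answered wrongly, since a sound origin is planned beside the faulty one. The primary objective, a count of patients, is untouched. The truncation does not depend on the prior-therapy condition, because survival to inclusion is required in any case. Severity: moderate, for a secondary objective.

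**What to change.** In section 6.1, state that all comparisons between alteration groups, both log-rank tests and prognostic models, count time from inclusion (sampling) or from the start of treatment after biopsy. Because section 4.2.1 allows a second biopsy when the first fails, the sampling date should be that of the sample that gave the profile. Report time from diagnosis to inclusion by group and use it as a baseline covariate.

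Drop the curves from initial diagnosis, or label them descriptive and conditional on survival to inclusion. Use delayed entry at most as a sensitivity analysis, with its independence assumption stated.

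The cost is a sentence or two and no new data: the dates of diagnosis, sampling, treatment start, and death or last contact are those the planned analyses already need. The price is that survival from diagnosis is no longer reported as an inferential result. The treatment-start origin also leaves out patients who start no treatment after biopsy, so the sampling origin is the one that covers every typed patient.

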#### **4.4 – Molecular analyses**

The molecular analyses will be carried out by the Molecular Oncology and Molecular Oncogenetics laboratories of the Paoli-Calmettes Institute. Real-time, weekly to bi-monthly analyzes will include testing for DNA copy number alterations and mutations, as well as assessing protein expression. These will concern genes of therapeutic interest that can be targeted by existing drugs or that predict the benefits of a particular systemic treatment. In our experience, it will take between 3 to a maximum of 5 weeks to obtain results (4 weeks in the SHIVA trial for the first 100 patients included). The DNA and RNA will be extracted according to a standard method and their integrity verified on gel and Agilent microarrays.

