## **4.5 – Patient care**

Patients who are candidates for this project will be given a specialized consultation. During the consultation, the informed consent form will be given to the patient. If the patient agrees to participate in the study (signs consent form), the taking of the samples will be scheduled according to the above description (4.2- biological sampling at inclusion). Once the molecular analyses have been carried out, all the clinical and molecular data will be presented and discussed during a multidisciplinary, weekly, medical/scientific MTB.

This study does not evaluate proposed treatments. Patient care and monitoring will therefore be carried out according to the procedures and practices of the associated center or the specificities of a clinical trial in which the patient could be included, according to the recommendations of the MTB. The patients will then be followed for a period of 3 years. Follow-up data (relapse, death, etc.) will be collected annually. If a cancer susceptibility gene is identified, specific and individualized care will be offered to the patient. This care will not be carried out as part of the study and will require the signing of another specific informed consent form.

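### Overall survival counted from initial diagnosis is left-truncated, because patients enter only at an advanced stage; ordinary Kaplan-Meier overstates it, and log-rank tests run from that origin can mislead

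*Protocol*

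**What the plan says.** Protocol section 6.1 names the endpoints and the method ("Overall survival and recurrence-free survival will be evaluated via the Kaplan-Meier method") and sets two time origins: "via the Kaplan-Meier method from the date of initial diagnosis and from the date of treatment start post-biopsy". It then adds: "Survival comparisons of different groups of molecular alterations will be performed using log-rank analysis". It does not say which origin those comparisons use, and it mentions no delayed entry or risk-set adjustment. Progression-free survival (PFS) appears in the prognostic analyses of 6.1 and in the secondary objective of 2.2, but not in the sentence that sets the origins.

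On entry, section 3.1 requires "Locally advanced or metastatic stage, with tumor lesion accessible for biopsy". The introduction to section III describes the patients as "progressive during at least one line of prior systemic therapy"; the list in 3.1 does not repeat this. Neither place limits the time since diagnosis. Section 4.5 puts sampling after consent ("If the patient agrees to participate in the study (signs consent form), the taking of the samples will be scheduled") and follows patients for 3 years. Section 4.2.1 allows a second biopsy when none of the samples can be profiled.

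**The concern.** A patient who died between diagnosis and inclusion cannot be in this cohort. Kaplan-Meier from diagnosis without delayed entry still counts that interval as time at risk, with no possibility of a death. The early hazard is diluted and the whole OS curve is lifted. This is left truncation.

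The same origin causes a different problem for recurrence-free survival. A patient who recurred before inclusion enters with the event already past, and is in the cohort partly because of it. That selection favours short recurrence-free times, so the bias can be downward.

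At stake is the secondary objective in 2.2 that links molecular alterations to PFS and OS. Section 6.2 adds 100 patients to strengthen the secondary-objective analyses. All cancer types are admitted, and locally advanced and metastatic disease are mixed, so the time from diagnosis to entry may well differ between alteration groups. Such a difference could pass for a prognostic effect.

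**Working it through.** **Inputs from the protocol.** Follow-up is 36 months from entry (4.5). There are 560 inclusions with 35% technical failure (6.2), so about 560 × 0.65 = 364 typed patients. The one sizing figure reproduces: 300 / 0.65 = 462 against the stated 460 (460 × 0.65 = 299). It has no bearing on survival.

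**Assumed inputs.** True OS from diagnosis is exponential with median M. The lag from diagnosis to potential entry is exponential with median L and independent of survival. Only patients alive at entry are kept, and nobody is lost before 36 months of follow-up.

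**Step 1: the naive curve at 36 months.** Let λ = ln 2 / M and μ = ln 2 / L. Among patients kept (T > lag),

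P(T > t | kept) = S(t) × [1 + (λ/μ)(1 − e^(−μt))], with S(t) = 2^(−t/M), λ/μ = L/M and e^(−μt) = 2^(−t/L).

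Nobody is censored before 36 months from diagnosis, so up to that time this is what ordinary Kaplan-Meier estimates.

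| M | L | True S(36) | Factor | Naive S(36) |
|---|---|---|---|---|
| 24 | 6 | 2^(−1.5) = 0.354 | 1 + 0.25 × (1 − 2^(−6)) = 1.246 | 0.441 |
| 24 | 12 | 0.354 | 1 + 0.5 × (1 − 2^(−3)) = 1.438 | 0.508 |
| 24 | 24 | 0.354 | 1 + 1 × (1 − 2^(−1.5)) = 1.646 | 0.582 |
| 36 | 12 | 2^(−1) = 0.500 | 1 + (1/3) × (1 − 2^(−3)) = 1.292 | 0.646 |

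**Step 2: naive medians.** These come from 60 simulated cohorts of 560 per scenario, censored 36 months after entry.

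| M | L = 6 | L = 12 | L = 24 |
|---|---|---|---|
| 24 | 31.7 (+32%) | 36.9 (+54%) | 42.7 (+78%) |
| 36 | 44.0 (+22%) | 50.7 (+41%) | 60.4 (+68%) |

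Hand check at M = 24, L = 6, t = 31.7: 2^(−31.7/24) = 0.400; factor 1 + 0.25 × (1 − 2^(−31.7/6)) = 1.244; product 0.498, so about one half.

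**Step 3: does delayed entry remove it?** A separate large simulation, indexed by mean rather than median lag (12 / 24 / 36 months):

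| True median | Naive median | Delayed-entry median |
|---|---|---|
| 24 | 33.7 / 39.5 / 43.2 | 23.9 / 24.0 / 23.8 |
| 36 | 46.7 / 54.6 / 61.3 | 35.9 / 35.9 / 35.5 |
| 60 | 72.3 / 85.9 / 98.7 | 59.8 / 59.8 / 59.7 |

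Timing from entry recovered 35.7 to 35.9 for a true 36, so a clock that starts at entry shows no inflation in this model.

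**Step 4: log-rank from diagnosis.** An illustrative 100 against 264 typed patients, true median 36 months in the reference group, two-sided 5% level:

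| Scenario | Naive rejection | Delayed-entry rejection | Naive HR | Delayed-entry HR |
|---|---|---|---|---|
| No difference, equal lag | 4.5% | 3.7% | 1.00 | 1.00 |
| No difference, mean lag 18 v 30 | 19.9% | 4.6% | 1.21 | 1.00 |
| No difference, mean lag 12 v 36 | 61.7% | 5.3% | 1.53 | 1.01 |
| True HR 1.5, equal lag | 84.8% | 75.4% | 1.64 | 1.55 |

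**Step 5: recurrence-free survival from diagnosis.** With an assumed true median of 60 months and a mean entry time of 48 months, patients who had recurred before entry show a median of 21 months. This is the extreme case in which everyone had already recurred. It shows the direction and is not an estimate for this cohort.

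**The case against.** The strongest reply is that survival is only part of one secondary objective, carries no power claim, and could be handled in a SAP that is not shown. The point about weight stands. The point about the SAP stands only in part: a SAP could add risk sets, but the protocol itself fixes the origin and names the methods without them.

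Three stronger readings are tempting, and the documents support none of them.

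- **Every curve is inflated.** A reader might infer this, but 6.1 also plans curves from the start of treatment after biopsy. That clock starts after entry and carries no guaranteed time since diagnosis. For recurrence-free survival from diagnosis the bias can go the other way. Inflation is established for OS from diagnosis only.
- **The comparisons by alteration are bound to be wrong.** With equal lags and no true difference, the naive test kept its level (4.5%, HR 1.00). With a true HR of 1.5 and equal lags, the naive HR was 1.64 against 1.55 with delayed entry. False positives need a lag that differs between groups. The protocol neither shows such a difference nor says that these tests start at diagnosis.
- **The treatment-start origin loses patients who die while awaiting results.** Section 4.4 says "it will take between 3 to a maximum of 5 weeks to obtain results", but that is laboratory turnaround. Section 6.1 says only that treatment starts after biopsy, and nothing requires it to wait for the report. What remains is that these curves describe patients who start treatment, not everyone included.

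The sizes rest on assumed medians, lags and exponential forms, and the description of patients as previously treated rests on the introduction to section III alone.

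**Conclusion.** The defect is real and confined to a secondary objective. As written, OS from initial diagnosis is left-truncated and will be overstated: by about 20% to 80% in the median for true medians of 24 to 36 months and median lags of 6 to 24 months, assuming exponential survival and a lag independent of survival. The direction follows from the entry rule; the size depends on these assumptions. Recurrence-free survival from diagnosis does not suit this population. Log-rank tests would be biased if they were run from diagnosis and the lag differed between groups.

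This should be fixed, but it does not threaten the trial. The primary objective is a count of patients, and neither it nor the 460/560 sample size depends on survival.

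**What to change.** Reword section 6.1:

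1. If OS from initial diagnosis is kept, analyse it with delayed entry and label it descriptive. Patients join the risk set at inclusion or, for comparisons by alteration, at the biopsy that produced the profile. Delayed entry assumes that entry time is independent of survival, which is doubtful when patients enter on progression; this is one more reason for the label.
2. Drop recurrence-free survival from diagnosis.
3. Run the log-rank and prognostic analyses of OS and PFS in typed patients from the profile-yielding biopsy (or with delayed entry), and state that origin. Inclusion and this biopsy need separate dates: sampling follows consent, and a patient typed only at a second biopsy had to survive to it. At the planned 35% failure rate, about a third of included patients have no molecular group and cannot enter these comparisons.
4. Present treatment-start curves as an analysis of treated patients, with the number never treated.

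Cost: no extra patients. Reported OS from diagnosis becomes less favourable, and its early part rests on smaller risk sets. Section 4.3 does not list the dates collected, so confirm that diagnosis, inclusion, each biopsy and treatment start are all recorded.

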### **2.2 Secondary objectives**

- Define the molecular alterations of advanced malignant solid tumors.
- Compare the molecular portraits of metastatic samples with those of the primary tumor if available (heterogeneity, clonal expansion) and normal cells (somatic or constitutional mutations) from the same patient.
- Determine, for the most frequent diseases (such as breast cancer; lung cancer; gynecological cancers, such as cervical, endometrial, ovarian, and fallopian tube; urological cancer, such as prostate, kidney, and bladder; and digestive cancers, such

as colon, pancreatic, and liver), the relationship between these molecular alterations and the histological and clinical disease characteristics, including progression-free survival and overall survival.

- Perform pan-genomic molecular analysis on metastatic samples with full exome sequencing and transcriptome analysis (expression, fusion transcripts: DNA microarray, RNA-seq).
- Perform an analysis of circulating tumor DNA.
- In the case of breast cancer, validate preclinical models of therapeutic tumor response (xenografts, short-term culture, and organoids).
- In cases of breast and digestive cancer, validate the isolation and characterization of circulating tumor cells.

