##### 4.4.2 – Testing for mutations: targeted next-generation sequencing (NGS)

Mutations in genes of interest (around 370 selected genes, of which nearly 50 are "targetable" by existing drugs) will be identified via targeted next-generation sequencing (NGS). Two different technologies will be used: the PGM Ion Torrent system (Life Technologies) or the MiSeq platform (Illumina), with the HaloPlex kit (Agilent Technologies) including primers for the 370 genes of interest. The relevant medical literature will be monitored during the study in order to complement and update the list of genes coding for proteins of therapeutic interest.

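### Section 6.1 compares survival by alteration group without the per-disease scope of objective 2.2 or stratification by cancer, so an alteration that only marks cancer type can look prognostic

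*Protocol*

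**What the plan says.** Protocol section 6.1 gives the survival method in one sentence: "Survival comparisons of different groups of molecular alterations will be performed using log-rank analysis". The groups are defined by alteration. The sentence mentions no disease, stratum or covariate. For histological and clinical variables, 6.1 says the analysis "will be performed using chi-square or Fisher, Wilcoxon, or Kruskal-Wallis tests depending on the nature of the data collected", again without mention of disease. It closes with: "Prognostic studies on overall survival and progression-free survival will be performed at the end of the study", for which no method is given.

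The scope is set elsewhere. Section 2.2 frames the aim by disease: "Determine, for the most frequent diseases", followed by breast, lung, gynecological, urological and digestive cancers, each of the last three being a family of several organs. The eligibility section admits everyone: "All cancer types will be included whether they are common or rare cancers". Section 6.2 adds 100 patients, for a total of 560, to enlarge the subpopulations used for the secondary objectives.

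**The concern.** The objective is by disease, but the method section describes a comparison by alteration. Read alone, 6.1 would allow one curve for carriers and one for non-carriers across whatever cancers happen to be combined. Even an analyst who keeps to the groups in 2.2 would, in three of the five, put cancers from different organs into one comparison.

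This matters when alteration frequency and survival both vary by cancer. Carriers and non-carriers then differ in their mix of cancers, and a log-rank test without strata picks up that mix. The alteration would be reported as prognostic when it only identifies the cancer, which the clinician already knows. The chi-square, Fisher and rank tests are open to the same problem when a clinical variable also varies by cancer.

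**Working it through.** **Plan's own figures.** Section 6.2 wants 300 evaluable cases at 35% technical failure: 300 / (1 - 0.35) = 461.5, so 462 against the stated 460, which reproduces within rounding. The amended total gives 560 x 0.65 = 364 evaluable cases. Five equal disease groups (an assumption) would hold 364 / 5 = about 73 each.

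**Inputs.** From the protocol: 364 evaluable, 36 months of follow-up, log-rank test. Assumed, because the protocol gives none: median survival by cancer, prevalence of the alteration by cancer, cancers of equal expected size, exponential survival, two-sided 5% level. In every case the alteration has no effect within any cancer.

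**Mechanism by hand.** The monthly hazard is ln 2 / median. Take two equal cancers with medians of 8 and 16 months and prevalences of 5% and 30%.
- Hazards: 0.693/8 = 0.0866 and 0.693/16 = 0.0433.
- Carriers from the 8-month cancer: 0.05 / (0.05 + 0.30) = 14.3%. Non-carriers: 0.95 / (0.95 + 0.70) = 57.6%.
- Starting hazard, carriers: 0.143 x 0.0866 + 0.857 x 0.0433 = 0.0495.
- Starting hazard, non-carriers: 0.576 x 0.0866 + 0.424 x 0.0433 = 0.0683.
- Apparent hazard ratio at the start: 0.0495 / 0.0683 = 0.73, where the true value within each cancer is 1.

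**Test.** The statistic is (sum of O - E)^2 / (sum of V), referred to chi-square with 1 df. Unstratified, E and V use the carrier share among all patients at risk. Stratified, they are computed within each cancer and then summed.

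**Simulated rejection rates** (2,000 to 10,000 cohorts per case; at 4,000 the standard error of a 5% rate is sqrt(0.05 x 0.95 / 4000) = 0.3 points; ranges show repeat runs):

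| Case | Medians (months) | Prevalence, same order | Unstratified | Stratified |
|---|---|---|---|---|
| Pooled 364, two cancers | 8 / 16 | 5% / 30% | 43-46% | about 5% |
| Pooled 364, two cancers | 6 / 18 | 5% / 30% | 73-75% | 5-6% |
| Pooled 364, two cancers | 8 / 12 | 10% / 20% | 7-8.5% | 5-6% |
| Pooled 364, five cancers | 8 to 30 | 40% in the worst, 5% elsewhere | 73% | 5.4% |
| Pooled 364, five cancers | 8 to 30 | 15% in the worst, 5% elsewhere | 17% | 5.3% |
| Pooled 364, five cancers | 12 to 18 | 40% in the worst, 5% elsewhere | 14% | 4.9% |
| Pooled 364, five cancers | 12 to 18 | 15% in the worst, 5% elsewhere | 7% | 5.4% |
| Pooled 364, five cancers | 8 to 30 | 10% in all | 5.7% | 5.1% |
| One family of 73, three cancers | 24 / 8 / 12 | 10% / 50% / 10% | 25% | 5-6% |
| One family of 73, three cancers | 24 / 8 / 12 | 10% / 30% / 10% | 13% | 5-6% |

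Under mild imbalance, the family of 73 gave 6-7% unstratified against about 6% stratified. The equal-prevalence row is the control: without imbalance in prevalence there is almost no inflation.

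**The case against.** The best defence is that 6.1 is brief, not wrong. It does not say unstratified or pooled, and a stratified log-rank is still a log-rank analysis. Section 2.2 sets the question by disease, 6.2 recruits more patients to enlarge those subpopulations, and the all-cancers statement is an eligibility rule. Strata and covariates for secondary analyses are often left to a statistical analysis plan, which is not shown. The simulations rest on chosen medians and prevalences.

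Much of this stands. A reader might infer that the protocol plans a pooled all-cancer survival comparison. It does not, so the pooled rows show what 6.1 leaves open and not what 2.2 intends.

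A reader might also infer a planned screen of the whole sequencing panel, described as "around 370 selected genes, of which nearly 50 are" targetable, with 370 x 0.05 = 18.5 chance findings. The documents do not support this as a finding. The 370 is a panel size and not a number of tests, 6.1 speaks of groups of alterations, and no significance level is stated. Multiplicity control is also ordinary analysis-plan content. The same goes for a minimum carrier count and a covariate set.

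The defence does not remove the mismatch between objective and method. Keeping to 2.2 takes away most of the between-cancer confounding, but not the part inside the digestive, urological and gynecological families.

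**Conclusion.** The point holds as a cheap improvement to a secondary analysis. Section 6.1 names the test but not the per-disease scope that 2.2 requires, and following 2.2 literally still mixes cancers in three of its five named groups. The inflation ranges from negligible to severe and depends on assumptions about survival and prevalence. For a mixed family of 73 patients it is roughly 13-26% when both differ markedly between cancers and 6-7% when they differ little. For a pooled cohort it is about 7% to 75%. Stratification holds the error at about 5-6% in the cases tried.

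It would be too strong to say that the plan will produce false prognostic markers. That depends on how groups are combined and on imbalances the protocol does not quantify. The primary objective, a count of patients, and the 460/560 sample size are untouched.

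**What to change.** In section 6.1, state that comparisons of outcome between alteration groups are made within disease as defined in 2.2. State also that any comparison combining cancers, including within the digestive, urological and gynecological families, uses a log-rank test or Cox model stratified by individual tumour type. Apply the same rule to the association tests: run them within tumour type, or use stratified forms (Cochran-Mantel-Haenszel for counts, van Elteren for ranks). The exception is a test whose variable is tumour type itself.

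This needs only wording and data already collected. The cost is some power where strata are small: in a family of 73 with three equal cancers, each stratum has about 24 patients, and at 10% prevalence only two or three carriers. Strata with no carriers contribute nothing. Power is low there in any case: with 73 events, 5% prevalence and a hazard ratio of 2, an unstratified test at 5% has about 25% power. False-discovery control could usefully be considered for the statistical analysis plan, but it is a separate suggestion.
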